#### Economic analysis

The economic analysis will use patient level data on participant resource use over the 28 day period between randomisation and the final follow-up telephone call. This will be compared with outcomes measured at the 28-day follow-ups. The analysis will consider three perspectives: (1) the health care provider and personal and social services (NHS and PSS); (2) participants and their families, (3) societal cost of lost productivity due to time off work.

The costs associated with the NHS and PSS perspective will include: trial and prescription medication costs, and the costs associated with primary and secondary care consultations. Participant resource use will include travel to consultations, expenditure on over-the-counter medications, cost of extra domestic help and childcare, prescription payments, and loss of earnings. The impact on society due to time off work will be captured by participants’ reports of their own and their families’ absenteeism.

We will use the data listed above to construct a cost-consequences matrix comparing cost from the three perspectives with the full range of primary and secondary outcomes. We will estimate incremental cost-effectiveness ratios comparing the extra cost, from the NHS perspective, of treating participants in the intervention group, with the extra benefit gained. Benefit will be described as (i) reduced cough duration, defined as the percentage of participants in each group with a duration at least 20% lower than the mean duration of participants in the control group or (if 20% reduction in mean duration in the control group is less than 1 day) the percentage of participants in each group whose duration is at least 1 day less than the mean of those in the control group; and (ii) quality-adjusted life year (QALY) gain (QALY estimates will be based on responses to the EQ-5D-5 L).

Sensitivity analyses will be used to test the robustness of the results against assumptions made and bootstrapping will be used to estimate the level of uncertainty around the estimates of cost per QALY.

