### Sample size calculation

Since the distributions of both primary outcome variables (the duration of moderately bad or worse cough and the mean severity score of all its associated symptoms on days 2 to 4 post-randomisation) will be positively skewed, sample size calculations are based on the log-normal distribution.

The mean (standard deviation (SD)) duration of bad or moderately worse cough was taken from a previous study examining the effectiveness of prescribed antibiotics for acute LRTI [5] and estimated as 5.8 (4.1) days. The mean (SD) symptom severity score between days 2 and 4 taken from the same trial was estimated as 2.3 (1.1). Using standard formulae for the mean and standard deviation of a log-normal distribution, this corresponds to 1.555 (SD 0.637) log days (or geometric mean of 4.74 days) for the cough duration outcome and 0.73 (SD 0.454) on the log scale (or geometric mean of 2.08) for the symptom severity outcome.

To account for testing multiple primary outcomes a lower alpha was specified for the symptom severity outcome to ensure that the overall alpha for the two primary outcomes remains close to 5%. Moderately bad or worse cough has been shown to resolve within 7 days for 50% of patients, 14 days for 75% and 4 weeks for 90% of patients [5]. Therefore, since duration of cough lasts significantly longer than the period during which severity of symptoms are measured (days 2 to 4) and is capturing an element of the illness severity, duration of moderately bad or worse cough might be viewed as the slightly more clinically important outcome. For this reason alpha remained at 5% for duration of cough and was reduced to 0.1% for symptom severity.

Sample size was calculated based on a 20% reduction in the duration of cough, corresponding to a geometric mean in the active treatment group of 3.79 days (mean 1.333 log days). Allowing (conservatively) for 20% attrition, 218 participants will need to be randomised per arm to retain 174 at follow-up and achieve 90% power with a two-sided alpha of 0.05. Hence a total sample size of 436 is required.

For the symptom severity outcome, a final achieved sample size of 174 participants in each arm will provide 89% power to detect a reduction in symptom severity score between days 2 and 4 of 20%, corresponding to a geometric mean of 1.66 units in the active group (mean 0.51 log units) with a two-sided alpha of 0.001.

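### Economic benefit (i) reduces cough duration to a percentage below 80% of the control mean: it responds to treatment but ignores days saved and loses about a fifth to a quarter of the information

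*Protocol article*

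**What the plan says.** The Economic analysis section plans cost-effectiveness ratios "comparing the extra cost, from the NHS perspective, of treating participants in the intervention group, with the extra benefit gained". Benefit is described in two ways. The second is QALY gain. The first, labelled reduced cough duration, is "the percentage of participants in each group with a duration at least 20% lower than the mean duration of participants in the control group". A fallback cut of one day below the control mean applies "if 20% reduction in mean duration in the control group is less than 1 day". The same section plans a "cost-consequences matrix comparing cost from the three perspectives with the full range of primary and secondary outcomes". It ties outcomes to the 28-day follow-up and promises bootstrapping for cost per QALY.

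The Sample size calculation section says that "the distributions of both primary outcome variables" "will be positively skewed, sample size calculations are based on the log-normal distribution". Cough duration is "estimated as 5.8 (4.1) days", converted to "1.555 (SD 0.637) log days (or geometric mean of 4.74 days". The planned effect is a 20% reduction. The same section also describes moderately bad or worse cough as resolving by 7, 14 and 28 days in 50%, 75% and 90% of patients.

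**The concern.** The 20% in the primary research question is a difference between groups. In the economic analysis it becomes a rule applied to each person. Because durations are skewed, 80% of the mean lies close to the control median, so about half of the untreated patients count as having a reduced duration with no treatment effect at all. The rule also scores someone who just crosses the cut the same as someone who gains many days, and gives nothing for a gain that stays on one side of it. The resulting ratio is a cost per extra person below a cut that the control data set. The trial studies days of cough, so a decision-maker would more naturally want a cost per day avoided. Dichotomising also makes the denominator of the ratio less precise.

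**Working it through.** **Inputs** (Sample size calculation): mean 5.8, SD 4.1 days, log-normal; 20% reduction; 174 analysed per arm; two-sided alpha 0.05.

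**1. Reproduce the plan.**
- σ = √ln(1 + (4.1/5.8)²) = 0.637.
- μ = ln 5.8 − σ²/2 = 1.555; geometric mean e^1.555 = 4.74.
- With a log difference of 1.555 − 1.333 = 0.222, n = 2(1.960 + 1.282)² × 0.637²/0.222² = 173.0, rounded up to 174 per arm. 174/0.8 = 217.5, so 218.

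All agree with the article.

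**2. The cut and who meets it.**
- Cut = 0.8 × 5.8 = 4.64 days. The fallback is not triggered, since 20% of 5.8 is 1.16 days.
- Control: Φ((ln 4.64 − 1.555)/0.637) = Φ(−0.032) = 48.7%.
- Active, with every duration multiplied by 0.8: Φ((ln 5.8 − 1.555)/0.637) = Φ(0.318) = 62.5%.
- Difference: 13.8 percentage points.

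A gamma or Weibull distribution with the same mean and SD gives a control share of 47% to 48%. A normal distribution would give 39%, so skew adds about 10 points.

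**3. Where the days saved lie under a uniform 20% reduction.** Days saved are proportional to untreated duration T. The share of all days from patients with T ≤ x is Φ((ln x − μ)/σ − σ).
- T ≤ 4.64 (already below the cut): Φ(−0.669) = 25%.
- 4.64 < T ≤ 5.8 (cross the cut): Φ(−0.318) − Φ(−0.669) = 37.5% − 25.2% = 12%.
- T > 5.8 (stay above the cut): about 62%.

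**4. Precision of the percentage.** SE = √[(0.487 × 0.513 + 0.625 × 0.375)/174] = 0.0528. Expected z = 0.138/0.0528 = 2.61; power Φ(2.61 − 1.96) ≈ 74%.

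**5. Precision of mean days restricted to 28.** With k = (ln 28 − μ)/σ, the mean is e^(μ+σ²/2) Φ(k − σ) + 28(1 − Φ(k)).
- Control 5.78 (SD 3.98); active 4.64 (SD 3.24); difference 1.15 days.
- SE = √[(3.98² + 3.24²)/174] = 0.389; z = 2.95; power ≈ 84%.
- Applying the 28-day limit to the percentage as well leaves its z at 2.61.
- Information lost: 1 − (2.61/2.95)² ≈ 22%.

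**6. The other description of duration.** Assume a log-normal with median 7 days, and take the log SD from the 14-day percentile (ln 2/0.674 = 1.03) or the 28-day one (ln 4/1.282 = 1.08). With durations capped at 28 days, the cut is about 8 days and about 55% of controls meet it. Expected z is 1.60 against 1.85, or 1.52 against 1.76. Information lost is about 25% either way.

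**7. The cut is itself estimated.** Its standard error is about 0.8 × 4.1/√174 = 0.25 days. Duration is counted in whole days, so sampling error alone can move the effective threshold by a day.

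**The case against.** A reader might infer that the percentage does not measure reduced duration at all, because half of the controls already meet it. The article does not support that. The ratio uses the extra benefit of intervention over control, so the background share is subtracted, and the planned effect moves the measure by 13.8 points.

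Nor is a control share near one half the source of the lost precision. A cut at 80% of the geometric mean (3.79 days, met by 36% of controls) gives practically the same power.

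A reader might also set the 74% power against the 90% planned for log duration, which would imply needing 272 rather than about 174 per arm. That overstates the loss here, because a log-scale difference is not a usable cost-effectiveness denominator; the fair comparator is a difference in mean days. The section plans no test of this ratio either, so power only stands in for precision.

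A control share of 62% to 63% follows from the 7/14/28-day percentiles only if durations are uncapped. On that uncapped basis the percentage is no less precise than the mean difference (z 1.56 against 1.50 with log SD 1.03). The advantage of mean days on those percentiles therefore depends on restricting to 28 days.

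Nor can it be said that durations beyond 28 days go unobserved: the outcome ascertainment and Participant follow-up sections provide for following cough to 8 weeks, by telephone and with permission. The Economic analysis section, however, ties its outcomes to 28 days.

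Finally, the cost-consequences matrix already sets costs beside cough duration, and a QALY ratio is planned. All of this stands and limits the point; none of it removes the coarseness of the measure.

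**Conclusion.** The point holds as a minor one. Benefit (i) detects shorter cough but does not quantify it: patients who cross the cut hold only about 12% of the days saved under a uniform 20% reduction, and about 62% of the days saved fall in patients who stay above it. The cut is met by about half of controls (49% at the planning inputs, about 55% on the alternative percentiles capped at 28 days) and is estimated from the control arm. Dichotomising costs about 20% to 25% of the information relative to restricted mean days.

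These figures assume log-normal durations, a proportional 20% effect in every patient and 174 analysed per arm; the 55% also assumes a log-normal fit to the stated percentiles. The primary clinical conclusions do not depend on this measure.

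**What to change.** Define benefit (i) as the between-group difference in restricted mean days of moderately bad or worse cough to day 28, and report cost per day avoided, with bootstrapped uncertainty as already promised for cost per QALY. Keep the percentage only as a descriptive summary, with a cut in days fixed before unblinding instead of one derived from the control arm.

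This changes the economic analysis wording and needs no new data, so completed recruitment is no obstacle. The cost is slightly more analysis and the loss of a simple percentage as the headline benefit.

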## Discussion

This paper describes a placebo-controlled, randomised multi-centre superiority trial that will establish the clinical and cost effectiveness of a commonly used treatment (corticosteroids) for an entirely novel indication and one of the commonest clinical problems managed in primary care: acute LRTI. The trial will recruit between 326 and 436 non-asthmatic adult patients presenting to primary care with an acute cough of less than 28 days duration and at least one other lower respiratory tract symptom or physical examination finding. Eligible, consented patients will be randomised to receive a 5-day course of either the active treatment (2 × 20 mg prednisolone daily) or matched placebo, and asked to complete a symptom diary for at least 7 and up to 28 days, depending on the duration of their illness. Participants will be telephoned weekly for 4 weeks, or until their cough resolves, up to a maximum of 8 weeks from recruitment.

## Trial status

The OSAC trial completed recruitment on 27 October 2014.

## Abbreviations

COPD: chronic obstructive pulmonary disease
CRF: case report form
GCP: Good Clinical Practice
GP: General Practitioner
LRTI: lower respiratory tract infection
NHS: National Health Service
OSAC: Oral Steroids for Acute Cough
QALY: quality-adjusted life year
SD: standard deviation
